## Abstract

**Background:**

Documented rates of dementia and cognitive impairment not dementia (CIND) in older Aboriginal and Torres Strait Islander Peoples is 3–5 times higher than the rest of the population, and current evidence suggests this condition is under-diagnosed and under-managed in a clinical primary care setting. This study aims to implement and evaluate a culturally responsive best practice model of care to optimise the detection and management of people with cognitive impairment and/or dementia, and to improve the quality of life of carers and older Aboriginal and Torres Islander Peoples with cognitive impairment.

**Methods/design:**

The prospective study will use a stepped-wedge cluster randomised controlled trial design working with 12 Aboriginal Community Controlled Health Services (ACCHSs) across four states of Australia. Utilising a co-design approach, health system adaptations will be implemented including (i) development of a best practice guide for cognitive impairment and dementia in Aboriginal and Torres Strait Islander communities (ii) education programs for health professionals supported by local champions and (iii) development of decision support systems for local medical software. In addition, the study will utilise a knowledge translation framework, the Integrated Promoting Action on Research Implementation in Health Services (iPARIHS) Framework, to promote long-term sustainable practice change. Process evaluation will also be undertaken to measure the quality, fidelity and contextual influences on the outcomes of the implementation.

The primary outcome measures will be rates of documentation of dementia and CIND, and evidence of improved management of dementia and CIND among older Indigenous peoples attending Aboriginal and Torres Strait Islander primary care services through health system changes. The secondary outcomes will be improvements to the quality of life of older Indigenous peoples with dementia and CIND, as well as that of their carers and families.

**Discussion:**

The Let’s CHAT Dementia project will co-design, implement and evaluate a culturally responsive best practice model of care embedded within current Indigenous primary health care. The best practice model of care has the potential to optimise the timely detection (especially in the early stages) and improve the ongoing management of people with dementia or cognitive impairment.

**Trial registration:**

ACTRN12618001485224. Date of registration: 04 of September 2019

## Background

### Introduction

The Australian population of Aboriginal and Torres Strait Islander peoples is growing, and the number of people aged over 65 years is projected to nearly double by 2026 [1]. Older Aboriginal and Torres Strait Islander Australians play a crucial role in the health of their communities, including as stewards of cultural rights and responsibilities for maintaining connections to Country, caring for extended family members, and providing leadership and support within their families and within communities [2]. Although there are many examples of Aboriginal and Torres Strait Islander Elders ‘ageing well’ [3], research has documented a high prevalence and incidence of dementia and cognitive impairment not dementia (CIND) in Aboriginal and Torres Strait Islander Australians living in urban, rural and remote regions of Australia [4–6]. Rates of dementia and CIND are up to 5 times those observed in the non-Indigenous population, with onset at younger ages, and are influenced by potentially modifiable risk factors such as head injury, cardiovascular disease and stroke. This is in contrast with other research internationally, that demonstrates a decrease in dementia rates in some developed nations in the last three decades [7, 8].

There is increasing evidence that prevention and management of vascular and other risk factors could delay progression of dementia [9], and this may be of particular relevance in Aboriginal and Torres Strait Islander communities where there are high rates of co-morbid conditions [10, 11] and onset at earlier ages, including past head injury – a key risk factor associated with decline from normal cognition to impairment [4], and other associations including age, stroke, non-aspirin analgesics, lower BMI, and higher systolic blood pressure (BP) [4]. In addition childhood trauma was found to be a contributor to cognitive decline in urban regions [6, 12].

To date no studies have been undertaken locally or internationally to address the needs of Aboriginal and Torres Strait Islander people with dementia and CIND through primary care, despite the alarmingly high rates of these conditions. The Let’s CHAT (Community Health Approaches To) Dementia program addresses the need to improve detection and management of dementia and CIND in primary care by using a holistic ‘real world approach’, based on adapting current systems and working collaboratively within ACCHSs and Communities to enable immediate translational outcomes. The program will co-design, implement and evaluate a culturally responsive best practice model of care embedded within current Aboriginal and Torres Strait Islander primary health care and ACCHS systems and services. This will optimise the timely detection (especially in the early stages) and ongoing management of people with dementia or its precursor CIND.

### Aims, objectives and outcomes of the study

The primary aim is to:

(i) Improve detection and management of dementia and CIND among older Aboriginal and Torres Strait Islander peoples attending primary care services through health system changes that include the following features:
Collaboratively developed education programs delivered for capability building of health practitioners including Aboriginal and Torres Strait Islander Health Workers, nurses and GPs. This program will be supported by local champions.Development of a culturally appropriate Aboriginal and Torres Strait Islander best practice guide (BPG) for dementia and CIND, and;Decision support systems including software modifications and adaptations of the current Aboriginal Health Check (Medical Benefit Scheme (MBS) 715) templates;

The secondary aims include improvement in the quality of life of carers and older people with dementia and CIND.

### Hypotheses

*Primary hypothesis*: Implementation of the Let’s CHAT Dementia model of care and health system changes will result in an increase in documentation of cognitive assessment and management for dementia and CIND in the clinic population aged 50 and over.

*Secondary hypothesis*: Compared with usual care, implementation of the Let’s CHAT Dementia model of care will: a) improve carers’ quality of life; and b) improve health outcomes and quality of life of those with CIND and dementia and help with health economic evaluation.

## Methods

### Design

This research project has adopted a stepped wedge cluster randomised controlled trial design with 12 clusters (ACCHSs) across four states of Australia. This method was chosen for pragmatic and ethical reasons - each cluster will experience the intervention over the course of the study, contamination of the groups prior to intervention is minimised due to geographic separation, and the design minimises the difficulties of implementing a program simultaneously over large distances [26, 27].

In the context of Indigenous research, a community participatory approach is essential to ensure the community, service providers and stakeholders are involved at all stages enabling successful translation into sustainable outcomes [28]. The CQI “plan, study, do, act” cycle will be utilised in combination with the i-PARIHS framework with the purpose of being a practical and familiar way to engage staff in practice change [29, 30]. The clinical and support staff within each ACCHS will be invited by the research staff to co-develop and participate in the implementation phase of the project – consisting of staff education and resource development. Additionally, staff from each ACCHS and local Community members will be recruited to act as project Ageing Well Champions (AWC) – co-researchers and leaders for change [24]**.** The primary role of AWCs will be to assist with implementing the Let’s CHAT Dementia model of care. They will be selected by ACCHS staff based on prior experience working with older Aboriginal and Torres Strait Islander Australian peoples. A protocol will be developed to outline the role of the champions.

A formal framework will be utilised to evaluate the nature and quality of the implementation, given the complexity of a multi-domain program and to determine barriers and enablers to care in a real-world health service intervention. In this project the iPARIHS framework has been selected to inform the knowledge translation aspects of the study [31]. This framework has been utilised for similar complex interventions in primary care and Aboriginal and Torres Strait Islander health care with successful outcomes [30]. iPARIHS adopts the following formula: *SI = Fac*^*n*^*(I + R + C)*, where examination and understanding of the Innovation (what is being implemented and the evidence base supporting it), the Recipients (who is exposed to the implementation both individually and collectively) and the Context (inner and outer) are crucial in determining the Successful Implementation of an intervention. The approach positions the notion of Facilitation as the underlying element for the enablement of successful implementation. This framework will marry well with the co-design approach being taken in this study; facilitation will be a key area of focus to promote ongoing engagement from staff in co-developing and taking ownership of the iteratively designed model of care [30].

### Setting

The study will be undertaken in North Queensland, New South Wales, Victoria and Western Australia with recruitment of three ACCHS in each state. Each health service (cluster) will be randomised to determine the sequence of commencement of education and resource provision (the implementation phase) and the ACCHSs will enter the implementation phase of the study at six-monthly intervals. Randomisation will be carried out by a statistician external to the project team. One ACCHS per state will begin the implementation phase at a time. Allocation concealment will be ensured until the second group of ACCHSs enters the intervention phase, at which time all ACCHSs will be aware of their allocation sequence. Blinding of trial participants (ACCHSs) and data collectors will not be possible, since both groups will be aware of and possibly engaged in the implementation activities taking place once a health service enters the intervention phase. However, the research team plans to recruit external outcome assessors to check data samples. Table 1 (below) outlines the expected timeline for each phase of the project.

**Table 1. Tab1:**
[figure not shown]
Project timeline

### Participants/recruitment

#### Organisations

Twelve ACCHSs in total will participate in the study, three from each state involved. The recruitment of the health care services is ensured as there are existing good relationships with the practices, built during previous research and collaborative projects. The 12 ACCHSs will be initially engaged through conversations between senior management staff and project investigators, with facilitation by peak bodies in some states.

#### Individuals

Patients identified through the medical record audit as having documentation of suspected or confirmed dementia or cognitive impairment and their carers will be approached to participate in a comprehensive geriatric assessment (CGA). The individual assessments will serve the dual purpose of enabling the measurement of individual outcomes across the course of the study and feeding back care recommendations for patient management from project geriatricians to ACCHSs and assisting with health economic evaluation. For each person suspected/identified as having cognitive impairment or dementia two case controls matched for age and gender will also participate in the CGA wing of the study. A known staff member or clinician from the ACCHS will make contact, inform the potential participants about the study and introduce a research staff member. The research staff member will then speak with the person/family to provide further information on the study and invite the person to participate.

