### Outcomes

The *primary outcome* is new documentation of dementia or CIND within healthcare records. This includes: (i) evidence of cognitive screening, and/or (ii) documentation of inquiry into cognitive health (e.g. asking questions regarding memory; obtaining informant report regarding cognition; (iii) laboratory or imaging investigations specifically requested for assessment of dementia. The data informing the primary outcome measure will be collected during regular audit cycles (detailed below), both prior to and during the project implementation phase.

*Secondary outcomes* are focused on improved health and well-being of older Aboriginal and Torres Strait Islander peoples with dementia, their carers and families. This will be measured through two validated quality of life tools in the CGA (refer below).

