### Dissemination and translation

Formal feedback of outcomes to health services personnel will occur every 6 months. Regular community updates will be provided through various culturally appropriate media, including newsletters and posters. Two workshops will be held (at baseline and on completion of the project) in each region for consumers, carers, health professionals, aged care workers and all other relevant stakeholders to provide and discuss information, present findings, and to set research priorities for the future. Ongoing translation strategies will be developed in collaboration with AWC and relevant stakeholders.

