### Comprehensive geriatric assessment (CGA) - client

Patients identified with possible dementia or CIND by audit and the gender and age matched case controls will be invited to be participants in the CGA. Different measures will be utilised in the CGA to gather data to assess individual outcomes throughout the life of the study. Cognition, quality of life, chronic pain, continence, daily function, mental health, history of psychosocial stress, nutrition, physical activity, sleep quality, frailty, visual and hearing impairment, muscle mass, blood pressure, grip strength and gait will be assessed (see summary table, Appendix 1, for standardised tools used). The CGA contains a detailed cognitive assessment section which includes the Kimberley Indigenous Cognitive Assessment, the Clock Test, Colour Trail Making Test and the Symbol Digit Modalities Test [39–42]. A semi-structured interview will be used to ascertain demographic factors, preferred language and education. Structured responses will be sought from the participants on the following: medical history, medications, past and present tobacco use (including chewing tobacco), past and present alcohol use, past and present drug use and history of head trauma. The CGA survey information will be collected by trained research assistants and will be entered and stored securely in REDCap. Paper copies will be stored in locked file cabinets in areas accessible by project research team members only.

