#### Sample size

Previous work in the Kimberley (confirmed by work in NSW) found that in Aboriginal and Torres Strait Islander communities, based on community screening, the true prevalence of dementia in people aged 45 years and over was approximately 10%, and the prevalence for cognitive impairment without dementia was also approximately 10% [5, 45]. Hence, the true prevalence of dementia or cognitive impairment in the relevant population is 20%. In the Kimberley, only 38% of those with dementia and only 3% of those with cognitive impairment had been diagnosed by primary health care practitioners. Moreover, the fraction of dementia cases identified by primary care in this work was likely to be higher than in standard practice as many of those with diagnosed dementia had been identified as part of previous research, with primary care practitioners subsequently notified. Therefore, we assume that no more than 15% of individuals with cognitive impairment or dementia are currently identified by primary health practitioners. The initial prevalence based on detection in primary care will be 15% of 20%, i.e. 3%. At a minimum, the study intervention should enable practitioners to identify at least half (50%) of the primary care patients with dementia or cognitive impairment. This would increase the prevalence based on detection in primary care to 50% of 20%, i.e. 10%. If an intraclass correlation of 0.01 and an average cluster size of 50 individuals is assumed, then the design effect will be 1.49. If the study was an individually randomised trial and we wished to detect an increase in the identification of cognitive impairment and dementia from 3 to 10% then the sample size would need to be at least 388 people (α = 0.05, power = 0.8). Therefore, the sample size required for this cluster randomised study will be 578 (388 × 1.49). Allowing for 10% drop-outs we plan to recruit 12 clusters of at least 55 people each, a total sample size of at least 660 individuals. Secondary outcomes compare the effect of earlier detection on scales of depression and stress and this sample size also has adequate power for these scales. We expect approximately 18 cases to be detected in the control period and 60 in the intervention period. The average cluster size will be 6.5 and assuming an ICC of 0.01, the design effect will be 1.055. Thus, our effective number of control cases will be 17 (18/1.055) and intervention cases 57 (60/1.055). Based on the variation found on the longitudinal data of carer strain in the Kimberley, our proposed study will provide over 80% power to find any clinically important effects.

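### The primary outcome has no rule for record entries that arise from the study's own cognitive assessments, and outcome feedback is not tied to crossover

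*Protocol article*

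**What the plan says.** **Outcome.** Under Outcomes, the primary outcome "is new documentation of dementia or CIND within healthcare records". Its listed components include "evidence of cognitive screening, and/or (ii) documentation of inquiry into cognitive health". The data come from audits held "both prior to and during the project implementation phase". Nothing distinguishes entries made by the service on its own initiative from entries that follow study activity.

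**Study testing.** Under Individuals, patients whose records already show suspected or confirmed impairment are invited to a CGA. For each of them, "two case controls matched for age and gender will also participate in the CGA wing of the study". The section on the client CGA states: "The CGA contains a detailed cognitive assessment section which includes the Kimberley Indigenous Cognitive Assessment". Table 2 places the participant CGA at baseline and 12-monthly.

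**Return of information.** The CGA serves two purposes, one of them "feeding back care recommendations for patient management from project geriatricians to ACCHSs". The carers/family CGA section repeats that a geriatrician reviews the assessments and that advice goes back to the service. Neither section limits this to services that have crossed over. CGA data are stored in REDCap, with paper copies in locked cabinets.

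**Outcome feedback.** Dissemination and translation states: "Formal feedback of outcomes to health services personnel will occur every 6 months". Which services this covers is not said. Element (ii) of the Intervention section uses the project's audit results, with feedback from each agency, to identify practice gaps.

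**The plan's own view of notification.** The Sample size section judges that Kimberley detection was probably above standard practice because "many of those with diagnosed dementia had been identified as part of previous research, with primary care practitioners subsequently notified". The Background reports that only 38% of dementia and 3% of CIND had been diagnosed or documented there even though the research team had told the GPs.

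**The concern.** A stepped-wedge comparison needs the control phase to show usual care, and needs the outcome to measure what the service does. Here the research team tests cognition while services are still waiting, and sends clinical advice to them. The outcome rule, applied as written, would count a resulting entry like any other. The matched controls matter most: they are not selected for documented impairment, so an entry for one of them could be new.

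The bias could go either way. Entries from control-phase CGAs would raise the control rate and dilute the contrast. If more people are flagged after crossover, more CGAs follow, and their entries would enlarge the contrast. Outcome feedback to waiting services would also expose them to something close to intervention element (ii) before they cross over.

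**Working it through.** **1. The plan's figure.** Inputs from Sample size: 3% versus 10%, α = 0.05 (taken as two-sided), power 0.80. With pooled variance and p̄ = 0.065:

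n per arm = [1.96·√(2·0.065·0.935) + 0.842·√(0.03·0.97 + 0.10·0.90)]² / 0.07² = 193.5, rounded up to 194. Two arms give 388, as stated. Design effect 1 + 49 × 0.01 = 1.49, and 388 × 1.49 = 578, as stated.

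**2. People tested by the study.** The plan expects 18 cases in the control period and 60 in the intervention period. These are 3% and 10% of 600 (12 clusters × 50).

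- Control phase: 18 × 2 = 36 matched controls, and 36/600 = 6%.
- Intervention phase: 60 × 2 = 120 matched controls, and 120/600 = 20%.

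The flagged cases are left out because they enter the CGA through documentation that already exists. A suspected case later confirmed could be an exception. Both figures are ceilings. They assume that everyone consents, all controls are in the audited sample, nobody is tested as a control in both phases, and every test is recorded and counted.

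**3. Dilution.** Let f be the share of control-phase tests in matched controls that reach the record and are counted. The documents do not give f. If only the control phase is affected, its rate is 3% + 6% × f. Power is computed with the method of step 1 at 194 per arm (578/1.49/2), against 10%.

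| f | Control rate | Difference (points) | Power |
|---|---|---|---|
| 0 | 3.0% | 7.0 | 0.80 |
| 0.10 | 3.6% | 6.4 | 0.71 |
| 0.25 | 4.5% | 5.5 | 0.55 |
| 0.50 | 6.0% | 4.0 | 0.31 |
| 1 | 9.0% | 1.0 | 0.05 |

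If both phases rise by the same amount (6% × f), the difference stays at 7 points. Power is then 0.72 (f = 0.25), 0.65 (f = 0.5) and 0.55 (f = 1), because the rates are higher.

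**4. Inflation.** If the same share f applies to the 20% in the intervention phase, the rates are 3% + 6% × f and 10% + 20% × f, and the difference is 7 + 14f points. At f = 0.25 this is 4.5% versus 15%, or 10.5 points. This route needs more people to be flagged after crossover, so it magnifies a real increase.

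**5. New diagnoses only.** Undetected impairment among undocumented people is (20% − 3%)/97% = 17.5%. Of 36 controls, about 6.3 would be impaired. If all gained a diagnosis entry, the control rate would be (18 + 6.3)/600 = 4.1% and power about 0.63. If only 38% did, the Background's figure for dementia, the gain is 6.3 × 0.38 = 2.4 people, or 0.4 points.

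All power figures are two-group approximations with one CGA round. A stepped-wedge model would give different values.

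**The case against.** The strongest reply is that the link from CGA to record is nowhere stated. CGA data go to a research database, and what returns to the service is advice on care, not test results. That stands. A reader might infer that the CGAs do generate outcome events; the text supports only that they can.

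A reader might also count three events per flagged case, giving 54 of 600 (9%) and 180 of 600 (30%). The document does not support this. The case is invited because documentation already exists, and the outcome is new documentation, so the matched controls are the main source.

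The Background is evidence against a large effect, since documentation stayed low despite notification. It concerns diagnoses, however. The outcome also counts screening and inquiry, for which no uptake figure is given. The Sample size section points the other way, so the share remains unknown.

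On outcome feedback, the dissemination section is brief and the timeline in Table 1 is not shown. It would be too strong to say that waiting services will receive it. What stands is that the text does not exclude it.

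Audit coding details may sit in a fuller document. But the article defines the primary outcome itself, and whether study-generated entries count is part of that definition.

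Lastly, excluding such entries has its own bias: a service has less reason to screen someone the study has just tested. This also stands, and is why both analyses are needed.

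**Conclusion.** The concern holds as a gap in the outcome definition. As written, the rule cannot separate a change in service practice from the study's own activity in the primary comparison. The potential size is material: ceilings of 6% and 20% of the cohort against a 7-point target, and power of about 0.55 if a quarter of control-phase tests in matched controls were counted in that phase alone. This rests on the assumptions that tests or advice reach the audited record and that matched controls are audited clients. Neither the actual share nor the direction of bias can be settled from the document. The lack of any limit on six-monthly outcome feedback is a second, separate gap, which does not depend on where CGA results are filed.

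**What to change.** 1. Add a source field to the audit tool: did the entry arise from a study CGA or geriatrician feedback, yes or no.
2. State under Outcomes that such entries do not count towards the primary outcome in either phase, and report a sensitivity analysis that counts them.
3. State under Dissemination and translation that cluster-level outcome feedback goes to a service only from its crossover. If the partnership commitments rule this out, acknowledge that the control phase includes audit feedback.

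The return of clinical recommendations for individual patients is left unchanged.

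**Cost.** There is a little more audit work. Source would be coded by auditors who know the service's phase. The primary analysis may under-count service screening in people the study has already tested, which the sensitivity analysis would show. Waiting services would receive audit feedback later: with three groups at six-monthly intervals, the last crosses 12 months after the first, plus any baseline interval, which the visible text does not give. The field should be in place before audits accumulate, because the source of an entry may be hard to recover afterwards.
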